### Data collection

In case the patients meet our criteria, all information, including the demography, clinical information, preoperative radiological data, intraoperative findings, and laboratory and TEG data, will be recorded on the case report form (CRF). After being discharged, all the patients were followed up on a regular basis by outpatient visit and on telephone 3 months and 6 months after primary hemorrhage, respectively. During each follow-up visit, the survival condition, mRS, ACCE, and medication will be recorded. If the patients feel unable to undergo radiological examination in the participating center, a follow-up cranial image will be required. Once radiological examination is completed, the patients’ imaging data will be transmitted to the Tiantan hospital (this center will work as an imaging interpretation center) to reconfirm several events, including SSICH, PIB, and postoperative ischemic disease. During the study, the researchers are required to protect privacy for the patients and ensure the confidentiality of their medical information. The information collection schedule is presented in Table 4.

### Data management

All data will be collected and stored using CRFs, and SHIP established a data management committee (DMC) in Tiantan hospital to monitor data quality and ensure data security. The clinical researcher associate (CRA) will make regular visit to each participating center to ensure the strict performance of research program. In case of any contradiction to the study protocol, the CRA will report this to the investigators promptly. Throughout this study, a summary meeting will be held every 3 months to discuss and solve any problem arising from the study or encountered by the patients.

## Results

China National Clinical Research Center for Neurological Diseases will be responsible for data analysis. Sample size was calculated by using PASS (Version 15, NCSS corporation, American). All sample size calculations were performed by conducting two-sided test, *α* = 0.05 and *β* = 80% (the degree of control = 80%). In this study, two comparison groups will be established, with the primary and secondary outcomes as the focus in this study. According to our unpublished data collected from 7 participating centers in 2019, for SSICH patients on LOAPT, the total mortality was about 30% for operated patients and 45% for the patients receiving conservative treatment, with the ratio of two groups reaching about 1:1.5. Moreover, for operated SSICH patients, the incidence of PIB was about 23% for patients on LOAPT and 10% for patient not on LOAPT, with the ratio of two groups reaching about 1:2.5. With regard to the primary outcome, our sample size was calculated as 196 (196 SSICH patients on LOAPT, operation group: *n* = 78; conservation group: *n* = 118). As for the secondary outcome, the sample size was 247 (247 operated SSICH patients, LOAPT group: *n* = 70; non-LOAPT group: *n* = 177). Moreover, in order to establish the coagulation function assessment system, the area under curve was expected to be 0.7, and the sample size was set to 92 (92 operated SSICH patients on LOAPT, PIB group: *n* = 23; non-PIB group: *n* = 69). In this case, a minimum of 387 SSICH patients (includes 118 patients on LOAPT receiving conservative treatment, 92 patients on LOAPT receiving emergency surgery, and 177 patients not on LOAPT receiving emergency surgery) may be required in this study to reach our research objective. Thus, to ensure final statistics, a total of 400 patients (patients on LOAPT receiving conservative treatment, *n* = 120; patients on LOAPT receiving emergency surgery, *n* = 100; patients not on LOAPT receiving emergency surgery, *n* = 180; Fig. 1) will be recruited. In this study, 10% of patients would be lost during follow-up. Finally, we decided to recruit 450 appropriate patients.

All statistical analyses were conducted with the assistance of SPSS (Version 22.0, IBM, American). The data was indicated as mean (x) ± standard deviation (SD) for normally distributed data, median, and interquartile range (IQR) for skewed distributed data or number (*n*) and percentage (%). In this study, two main comparative groups and an observational cohort will be established, as shown in Fig. 1. Firstly, in order to investigate the effect of emergency neurosurgery, a comparison will be performed between SSICH patients on LOAPT receiving conservative treatment and those receiving emergency neurosurgery. Secondly, in order to investigate the safety of emergency neurosurgery, a comparison will be performed between operated SSICH patients on LOAPT and those not on LOAPT. Thirdly, in order to investigate the intra/postoperative complications and the risk of ischemic disease after discontinuing antiplatelet treatment, the characteristics of SSICH patients on LOAPT will be analyzed; moreover, because the history of previous neural ischemic events or cardiac events could affect the risk of postoperative ischemic events, we would perform the subgroup analysis depending on this history to further investigate the effect of discontinuing antiplatelet treatment on the risk of ischemic disease. The difference will be compared by conducting χ^2^ test, Mann-Whitney *U* tests, or Student’s *t* tests. The independent risk factors were analyzed by logistic regression, while the factors with *p* < 0.10 in univariate analysis were entered into a multivariate logistic regression model. The result was indicated as odd ratio (OR) and 95% confident interval (CI). The receiver operating characteristic (ROC) curve analysis was performed to test the prediction value of different parameters and different methods. An area under the curve (AUC) in a ROC analysis of ≥ 0.7 is considered as a clinical utility, while *p* value of < 0.05 was treated as statistically significant.

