**Methods:**

As a multicenter and prospective cohort study, it will be conducted across 7 representative clinical centers. Starting in September 2019, the observation is scheduled to be completed by December 2022, with a total of 450 SSICH patients recruited. The information on clinical, radiological, and laboratory practices will be recorded objectively. All of the patients will be monitored until death or 6 months after the occurrence of primary hemorrhage.

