### Outcomes and study endpoints

All patients will be closely monitored until death or 6 months after the occurrence primary hemorrhage. In this study, the following outcomes will be taken into consideration (Table 3). The primary outcome is the total mortality, including in-hospital and out-of-hospital mortality. The second outcome is the postoperative hemorrhagic complication, and the PIB is our main focus. The functional outcome of patients is another outcome interesting us and will be assessed using modified Rankin scale (mRS). The postoperative adverse cardiovascular/cerebral events (ACCE) include the region of original stroke enlarging, new ischemic stroke occurring outside the operative region, myocardial infarction, repeated revascularization, and deep venous thrombus. The screening, evaluation, and follow-up schedules are detailed in Table 4.

**Table 3 Tab3:** Outcomes to be taken in consideration

(1) Total mortality; (2) postoperative hemorrhagic complication; (3) patients’ functional outcome; (4) postoperative adverse cardiovascular/cerebral events (ACCE).

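### The primary sample size of 196 does not give the stated 80% power: the protocol's own inputs need about 327 to 340 patients, and the planned 100 vs 120 gives about 63%

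*Protocol article*

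**What the plan says.** The section on outcomes and study endpoints defines the endpoint: "The primary outcome is the total mortality, including in-hospital and out-of-hospital mortality". The sample-size paragraph in Results gives every input needed to check the calculation:

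- **Test:** "All sample size calculations were performed by conducting two-sided test", with α = 0.05. Power is printed as β = 80% and glossed as "the degree of control = 80"%, which can only mean 80% power.
- **Rates for patients on LOAPT:** "the total mortality was about 30% for operated patients and 45% for the patients receiving conservative treatment".
- **Operated to conservative:** "with the ratio of two groups reaching about 1:1.5".
- **Result:** "our sample size was calculated as 196 (196 SSICH patients on LOAPT, operation group" 78, conservative 118).

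The same paragraph builds a minimum of 387 from "118 patients on LOAPT receiving conservative treatment", 92 operated patients on LOAPT and 177 operated patients not on LOAPT. It rounds this to a target of 400 (120, 100 and 180) and raises it to 450 for 10% loss to follow-up. The abstract repeats the last figure: "with a total of 450 SSICH patients recruited". The analysis paragraph names the χ² test for group differences.

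**The concern.** A 15-point difference around 40% mortality normally needs well over 300 patients for 80% power, so a total of 196 looks far too small. The figure also coincides with what the standard formula gives for the conservative group alone.

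Mortality is the outcome on which the effect of surgery is to be judged. At 63% power, a real reduction from 45% to 30% would miss significance in about 37% of such studies, against the 20% that the protocol claims. A reader who trusts the stated 80% would give a non-significant result more weight against surgery than it can bear.

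**Working it through.** **Inputs**, all from Results: p₁ = 0.30 (operated), p₂ = 0.45 (conservative), difference 0.15, k = n₂/n₁ = 1.5, z = 1.96 (two-sided 5%) and 0.8416 (80% power).

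**1. Can the printed 196 be reproduced as a total?**

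Unpooled variance:

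n₁ = (1.96 + 0.8416)² × (0.30×0.70 + 0.45×0.55/1.5) / 0.15² = 7.849 × 0.375 / 0.0225 = 130.8

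n₂ = 1.5 × 130.8 = 196.2, so the total is about 131 + 196 = 327.

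Pooled variance, with p̄ = (0.30 + 1.5×0.45)/2.5 = 0.39:

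n₁ = [1.96 × √(0.39×0.61×(1 + 1/1.5)) + 0.8416 × √0.375]² / 0.0225 = (1.234 + 0.515)² / 0.0225 = 136.0

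n₂ = 204.1, so the total is about 340 (343 if the smaller group is rounded up to 137 before applying the ratio).

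Other variants do not reach 196 either:

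| Variant | Total |
|---|---|
| Arcsine, two-sided, 1:1.5 | 337 |
| Continuity-corrected, two-sided, 1:1.5 | 368 |
| Two-sided, 1:1 | 326 to 352 |
| One-sided, 1:1.5 | 258 to 295 |
| Log-rank, two-sided | about 296 to 362 |
| Log-rank, one-sided | about 233 to 285 |

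**2. Where 196 probably comes from.** The unpooled formula puts 196.2 in the conservative group. Dividing 196 in the ratio 1:1.5 gives 196/2.5 = 78.4 and 117.6, which are the printed 78 and 118.

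The secondary calculation (PIB 23% vs 10%, ratio 1:2.5) behaves the same way:

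n₁ = 7.849 × (0.23×0.77 + 0.10×0.90/2.5) / 0.13² = 99.0; n₂ = 2.5 × 98.97 = 247.4; total about 346.

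The protocol prints 247 as the total. Split 1:2.5 this is 70.6 and 176.4, against the printed 70 and 177. One formula therefore gives both printed totals as the size of the larger group.

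**3. Power at the protocol's own group sizes** (30% vs 45%, two-sided 5%, pooled z-test, which matches the planned χ² test):

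Power = Φ{[0.15 − 1.96 × √(p̄(1−p̄)(1/n₁ + 1/n₂))] / √(0.21/n₁ + 0.2475/n₂)}

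For 78 vs 118: p̄ = (23.4 + 53.1)/196 = 0.390; Φ[(0.15 − 0.1395)/0.0692] = Φ(0.151) = 0.560.

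For 100 vs 120: p̄ = (30 + 54)/220 = 0.382; Φ[(0.15 − 0.1289)/0.0645] = Φ(0.327) = 0.628.

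| Operated vs conservative | Source | Power |
|---|---|---|
| 78 vs 118 | printed primary calculation | 56.0% (exact χ² 56.7%; unpooled 58%) |
| 92 vs 118 | minimum of 387 | 60.4% |
| 100 vs 120 | target of 400 | 62.8% (exact χ² 63.3%; unpooled 64%) |
| 112 vs 135 | all 450 analysed, in the proportions of the 400 | 67.9% |

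**4. What 100 vs 120 can detect.** With 45% in the conservative group, 80% power is reached when operated mortality is about 26.9%, a difference of 45 − 26.9 = 18.1 points.

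**5. The secondary comparison.** Power for 23% vs 10% is about 74% at 70 vs 177 and about 82% at the planned 100 vs 180.

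**The case against.** No formula or program output is shown, so the explanation that one group was read as the total is an inference. It also needs the unpooled formula. A mistyped rate is another possibility, since 30% vs 50% gives about 80% power at 78 vs 118. This is fair, and the cause should be described as probable. The shortfall does not depend on it, because the protocol states 45%.

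The recruitment figures rest only partly on 196. Of the 387, only the 118 comes from it; the 92 comes from the ROC calculation and the 177 from the PIB calculation. The planned numbers also already give the PIB comparison about 82% power. Both points stand, and they confine the lasting problem to the primary comparison.

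The power figures are for an unadjusted comparison, whereas this is a non-randomised cohort with multivariable logistic regression also planned, and the assumed rates are approximate. That is a proper caveat, but the protocol's own calculation is equally unadjusted.

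The analysis paragraph already plans odds ratios with 95% confidence intervals, and nothing in the protocol says that a non-significant result will be read as no effect. The risk of misreading therefore comes from the 80% claim, not from a stated rule. The β notation is a slip whose meaning is clear.

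The article being a condensed account does not help here: it prints a complete calculation whose result disagrees with its inputs.

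**Conclusion.** The concern holds. On the stated inputs, 80% power for total mortality needs about 327 to 340 patients on LOAPT, not 196. Power is about 56% at the printed 78 vs 118, about 63% at the planned 100 vs 120, and about 68% at best if nobody is lost. No standard variant of the calculation tried gives 196 as a total.

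These figures assume mortality of 30% and 45%, a two-sided 5% test and no covariate adjustment. The 63% refers to 100 and 120 analysed patients, since the 10% loss is added afterwards. That the larger group was mistaken for the total is very likely but not shown. The secondary calculation appears to carry the same slip, but the planned numbers cover it.

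**What to change.** In the sample-size paragraph of Results:

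- Replace 196 (78 + 118) by about 327 to 340 (131 + 196 to 136 + 204), naming the formula used.
- State that the planned 100 vs 120 gives about 63% power for 30% vs 45% in an unadjusted comparison, and that 80% power is reached only for a difference of about 18 points (about 27% vs 45%).
- Limit the statement that 387 patients meet the research objective, since this is not true of mortality at 80% power.
- Correct the secondary total of 247 in the same way, and note that the planned 100 vs 180 gives about 82%.
- Print power = 80% in place of β = 80%.
- Add that the primary comparison will be interpreted from its estimate and confidence interval, and that non-significance will not be taken to show that surgery has no effect.

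The cost is one recalculation and a few sentences. Recruitment can stay as planned; the price is a less favourable, but correct, power statement.

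### The stated PIB sample size of 247 (70 + 177) gives about 74% power by the chi-square test, not the stated 80%; the planned 100 vs 180 does reach 80%

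*Protocol article*

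**What the plan says.** The sample size paragraph in the Results section of the protocol article sets common conditions: "All sample size calculations were performed by conducting two-sided test", with alpha 0.05. The 80% is printed as a value of β but can only sensibly be read as power. For PIB among operated patients it gives "the incidence of PIB was about 23% for patients on LOAPT and 10% for patient not on LOAPT". Group sizes are assumed to stand at about one LOAPT patient to 2.5 others. The result is a total of 247 ("As for the secondary outcome, the sample size was 247 (247 operated SSICH patients, LOAPT group"), which the article divides into 70 patients on LOAPT and 177 without it.

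The paragraph then builds a minimum of 387 from three cells: 118 LOAPT patients treated conservatively, 92 LOAPT patients operated on, and 177 non-LOAPT patients operated on. The 92 comes from the AUC calculation for the coagulation assessment system, and the 177 from the PIB calculation. The cells are rounded up to 120, 100 and 180 (total 400). Recruitment is then set at 450, with 10% loss to follow-up expected.

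For the analysis, the next paragraph of the same section says "The difference will be compared by conducting χ^2^ test", with Mann-Whitney and t tests as the alternatives. For a binary outcome such as PIB, the chi-square test is the one that applies.

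**The concern.** A total of 247 looks too small for a 13-point difference at an uneven ratio. Every input is printed, so the figure can be checked directly.

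PIB is the main focus of the secondary outcome, and operated LOAPT against operated non-LOAPT patients is the comparison by which the study judges the safety of surgery. A reader who accepts 70 vs 177 would believe that size has a 20% chance of missing the assumed difference, when the chance is 26% (pooled) to 35% (unpooled). The 177 also passes into the 387 minimum, so the derivation of the overall size rests partly on a figure that does not follow from its inputs.

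**Working it through.** **Inputs (Results section).** p1 = 0.23 (LOAPT), p2 = 0.10 (non-LOAPT), difference 0.13, k = 2.5, two-sided alpha 0.05 (z = 1.960), power 80% (z = 0.842). Variances: 0.23 × 0.77 = 0.1771 and 0.10 × 0.90 = 0.0900.

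**1. Attempt to reproduce 247 as a total at 1:2.5**

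*Unpooled:* n1 = (1.960 + 0.842)² × (0.1771 + 0.0900/2.5) / 0.13² = 7.849 × 0.2131 / 0.0169 = 98.97, and n2 = 2.5 × 98.97 = 247.4. Rounded up, 99 + 248 = 347.

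*Pooled:* p̄ = (0.23 + 2.5 × 0.10)/3.5 = 0.1371, and p̄(1 − p̄)(1 + 1/2.5) = 0.1657. Then n1 = [1.960 × √0.1657 + 0.842 × √0.2131]² / 0.13² = 1.407 / 0.0169 = 83.3, and n2 = 208.2. Rounded up, 84 + 209 = 293, or 84 + 210 = 294 if the ratio is kept exactly.

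*Other two-sided variants:* log odds ratio about 284, arcsine about 303, pooled with continuity correction 329. None gives 247. The one-sided totals tried (pooled 235, arcsine 238, continuity-corrected 270) do not give it either.

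**2. Where 247 may come from**

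The unpooled *larger group* is 247.4. Dividing 247 by 1:2.5 gives 70.6 and 176.4, close to the stated 70 and 177. The primary outcome (30% vs 45%, 1:1.5) shows the same pattern. There the unpooled smaller group is 7.849 × (0.21 + 0.2475/1.5)/0.15² = 130.8 and the larger is 196.2. The stated total is 196, and 196 split 1:1.5 is 78.4 and 117.6, against the stated 78 and 118. Both totals are thus consistent with a larger-group size having been taken as the total.

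**3. Power at the stated and planned sizes**

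Pooled power = Φ[(0.13 − 1.960 × SE0)/SE1]; unpooled power = Φ[0.13/SE1 − 1.960]. SE0 is the standard error under the pooled rate and SE1 the one under the two separate rates.

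| LOAPT / non-LOAPT | SE0 | SE1 | Pooled (chi-square) | Unpooled |
|---|---|---|---|---|
| 70 / 177 (stated for PIB) | 0.0485 | 0.0551 | 73.7% | 65.5% |
| 92 / 177 (in the 387 minimum) | 0.0452 | 0.0493 | 80.0% | 75.0% |
| 100 / 180 (planned) | 0.0441 | 0.0477 | 82.0% | 77.9% |

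Exact binomial enumeration of the chi-square test gives 73.7%, 80.7% and 82.6% for the three rows. At 70 vs 177, Fisher's test gives 70.9% and the continuity-corrected test 68.6%.

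**4. Loss to follow-up**

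400/0.9 = 444.4, and 450 × 0.9 = 405. The 100 and 180 belong to the 400, which is the number left after the 10% allowance.

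**The case against.** The strongest reply is that 247 is an intermediate figure that later cell sizes supersede. The article takes the larger requirement for the operated LOAPT cell and shows this openly: the AUC aim needs 92, and 92 is what enters the minimum. Under the chi-square test the article names, both the minimum and the plan meet 80%. This stands, and it limits the point to a wrong stated figure. What remains is that the article presents 70 vs 177 as sufficient for 80% power and never gives the PIB power at the sizes it will use.

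A reader might infer more in four ways that the documents do not support:

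- *That the PIB comparison to be run is underpowered.* By chi-square, 100 vs 180 gives 82%. Only the unpooled formula falls short, by about 2 points, and it does not match the named test.
- *That 10% loss would cut 100 and 180 further.* Recruitment is raised from 400 to 450 to cover it, so this would subtract the loss twice.
- *That the larger-group slip is established.* The article does not describe the step. The fit is close but not perfect (247 splits to 71/176 by rounding), and a 1:1 unpooled total of 248.1 would explain 247 about as well. The 1:1 total for the primary outcome is about 319, though, not 196, so of these two explanations only the larger-group one fits both. The power shortfall does not depend on which is true.
- *That this is the study's only safety comparison.* The Study design section also compares complications between operated and conservatively treated LOAPT patients, and adverse cardiovascular/cerebral events are a listed outcome.

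One-sided pooled power at 70 vs 177 would be 81.9%, but the article says that all calculations were two-sided.

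**Conclusion.** The point holds for the stated figure. At the article's own inputs, 247 (70 + 177) has about 74% power by chi-square and about 65% unpooled, against a stated 80%. The total needed at 1:2.5 is about 293–294 (pooled) or 347 (unpooled), so 247 is about 46–47 or 100 patients short.

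It does not hold against the planned comparison, which reaches about 82% by chi-square at 100 vs 180. That adequacy depends on the operated LOAPT group having been enlarged from 70 to 92 and then 100 for a different aim. The conclusion assumes the printed 80% means power, the PIB rates are as stated, and the 10% loss is covered by recruiting 450.

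**What to change.** 1. Correct 247 (70/177) to about 84 + 210 = 294 (pooled chi-square) or 99 + 248 = 347 (unpooled) at 1:2.5, and name the test and variance formula used.
2. Stop using 70/177 as a basis for the 387 minimum. Justify the PIB comparison by the cells actually planned: about 80% power at 92 vs 177 and about 82% at 100 vs 180 by chi-square (75% and 78% unpooled). The planned ratio is 1:1.8 (180/100), so the 1:2.5 requirement need not be carried cell by cell into the total.
3. State that this power depends on the operated LOAPT group being enlarged for the AUC aim, and that 100 and 180 are evaluable numbers after the 10% loss allowance.

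The cost is one recalculation and a few sentences. No extra patients are needed for this comparison.

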**Fig. 1 Fig1:**
[figure not shown]
Research flow chart

In order to achieve the research objective, it is necessary to recruit all SSICH patients except those not on LOAPT receiving conservative treatment. The inclusion and exclusion criteria are detailed in Tables 1 and 2, respectively. Three cohorts, including two comparative groups and one observational group (Fig. 1), will be established. Firstly, in order to measure the effect of emergency surgery, a comparison will be drawn of the outcomes and complications between SSICH patients on LOAPT receiving emergency surgery and those receiving conservative treatment. Secondly, in order to evaluate the safety of emergency surgery, hemorrhagic complications will be compared between operated SSICH patients who are on LOAPT and those not on LOAPT. Thirdly, the clinical characteristics and coagulation function of SSICH patients on LOAPT will be analyzed to assess the risk of developing ischemic diseases after discontinuing antiplatelet treatment, based on which an effective approach to the assessment of coagulation state will be established for surgery.

**Table 1 Tab1:** Inclusion criteria

Inclusion criteria: (1) 18–75 years old; (2) non-traumatic intracerebral hemorrhage; (3) severe intracerebral hemorrhage, which was defined as patients with supratentorial bleeding volume > 30 ml, infratentorial bleeding volume > 10 ml, midline shift > 1 cm, or large intraventricular hematoma; (4) Glasgow coma score (GCS) < 13; (5) family members agree to provide an informed written consent.

**Table 2 Tab2:** Exclusion criteria

Exclusion criteria: (1) patients had cerebrovascular diseases, e.g., intracranial aneurysm or vascular malformation, and intracranial tumors, which were associated with hemorrhage; (2) hemorrhagic transformation of cerebral infarction; (3) hemorrhage caused by venous thrombosis; (4) patients with severe coagulation disorder, e.g., hemophilia; (5) patients with coagulation dysfunction caused by malignant tumor, hypohepatia, renal dysfunction, thrombocytopenia, coagulation diseases, and so on; (6) patients receiving other anticoagulation medications (vitamin K antagonist and new oral anticoagulants); (7) patients not on LOAPT who receive conservative treatment; (8) the patients who died before or on arriving at the hospital and within a short period (6 h) after admission.	

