### Qualification of participating center

To avoid participant bias while ensuring the sufficient number of cases included to reach our conclusion, all patients were recruited at the same time, and 7 neurosurgical centers were carefully selected considering the following criteria. Firstly, each center covers at least two communities or works as referral units for hemorrhagic stroke. Secondly, the center can carry out various treatment for SSICH, including all varieties of surgery and conservative treatment. Thirdly, the center is capable to admit more than 100 SSICH patients annually. According to an incomplete data, a total of 500 SSICH patients were evaluated across the 7 centers in 2019. Meanwhile, each center can fully represent the level of diagnosis and treatment of SSICH at a national level. Therefore, the centers involved in this study are considered representative.

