### Ethics and public involvement

Patients or the public were not directly involved in design or conduct of the study. This study was granted approval from Institutional Review Board of Beijing Tiantan Hospital, and the research would be conducted in strict accordance with the declaration of Helsinki and Human Biomedical Research Ethical Issues. In this study, researchers are not able to use randomized controlled trials; thus, all recruited SSICH patients will not be affected by normal course of diagnosis and treatment. When SSICH patients are included, they will be followed up until 6 months after the occurrence of primary hemorrhage.

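### The planned group sizes of 100/120/180 do not match the plan's own 2019 case mix of 1:1.5:2.5; at that mix 450 recruits give about 90 operated LOAPT patients (81 after 10% loss), short of the target of 100 and of the AUC aim's minimum of 92

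*Protocol article*

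**What the plan says.** All figures are in the sample-size paragraph of the Protocol article (Results).

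- **Case mix.** Data from the seven centres in 2019 give operated to conservative patients on LOAPT "with the ratio of two groups reaching about 1:1.5", and, among operated patients, on LOAPT to not on LOAPT "with the ratio of two groups reaching about 1:2.5".
- **Separate requirements.** Mortality: 196 (78 operated, 118 conservative). PIB: 247 (70 on LOAPT, 177 not). AUC aim: 92 operated LOAPT patients (23 with PIB, 69 without).
- **Combination.** The largest figure for each group is taken (92 + 118 + 177 = 387) and rounded to 100 + 120 + 180 = 400. After a 10% allowance for loss, "Finally, we decided to recruit 450 appropriate patients".

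Two other sections bear on how the groups fill. Study design (text after Fig. 1) says "it is necessary to recruit all SSICH patients except those not on LOAPT receiving conservative treatment". Ethics and public involvement says "all recruited SSICH patients will not be affected by normal course of diagnosis and treatment", which in context means that the study does not steer treatment. The article states no quota or closure rule for any group.

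**The concern.** The two ratios share the operated LOAPT group, so together they fix the expected mix of the whole cohort. The plan uses them to split 196 and 247. It then raises only the operated LOAPT group, from 78 to 92 and on to 100, and leaves the other two near their calculated sizes. In an observational cohort that takes all eligible patients, one group cannot be enlarged without enlarging the others in proportion or closing them earlier.

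At stake is the size of the operated LOAPT group. It serves both comparisons and is the whole sample for the coagulation assessment system. If the centres' mix holds, 450 recruits bring surplus non-LOAPT patients and too few operated LOAPT patients for the AUC aim.

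**Working it through.** **1. The plan's own total.** 400 / 0.9 = 444.4, so 445, rounded up to 450. This reproduces. The 400 is therefore the number wanted after loss, and 450 the number recruited.

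**2. Planned against reported mix.** Planned: 120/100 = 1.2 and 180/100 = 1.8. Reported: 1.5 and 2.5. No single total yields 100/120/180 at the reported ratios.

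**3. Groups expected from 450 recruits.** Operated LOAPT = 450 / (1 + 1.5 + 2.5) = 90. Conservative LOAPT = 1.5 × 90 = 135. Operated non-LOAPT = 2.5 × 90 = 225.

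| Group | Recruited | After 10% loss | Plan's minimum | Plan's target |
|---|---|---|---|---|
| Operated LOAPT | 90 | 81 | 92 | 100 |
| Conservative LOAPT | 135 | 121.5 | 118 | 120 |
| Operated non-LOAPT | 225 | 202.5 | 177 | 180 |

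Only the operated LOAPT group falls short.

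**4. Sensitivity to ratios given as approximate.**
- 1.45 and 2.45: 450/4.9 = 91.8 (82.7 after loss).
- 1.55 and 2.55: 450/5.1 = 88.2 (79.4 after loss).
- To reach 92, the two ratios may sum to at most 450/92 − 1 = 3.89 without loss, or 405/92 − 1 = 3.40 with it. The reported sum is 4.0.

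**5. Recruitment needed at the reported mix.** For 92 after loss: 92 × 5 / 0.9 = 511.1, so 512. For 100 after loss: 100 × 5 / 0.9 = 555.6, so 556.

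**6. Effect on the AUC aim.** Hanley-McNeil variance for AUC A, with n₁ PIB and n₂ non-PIB patients:

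Var(A) = [A(1 − A) + (n₁ − 1)(A/(2 − A) − A²) + (n₂ − 1)(2A²/(1 + A) − A²)] / (n₁n₂)

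Power = Φ[(0.2 − 1.96 × SE(0.5)) / SE(0.7)], two-sided 5%, since the plan says "All sample size calculations were performed by conducting two-sided test". The null value of 0.5 is my assumption; the article gives only the expected 0.7. The PIB rate is the plan's 23% throughout.

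| Operated LOAPT | PIB / non-PIB | SE(0.5) | SE(0.7) | Power |
|---|---|---|---|---|
| 81 | 18.6 / 62.4 | 0.0767 | 0.0741 | 75% |
| 90 | 20.7 / 69.3 | 0.0727 | 0.0702 | 79% |
| 92 | 21.2 / 70.8 | 0.0719 | 0.0694 | 80% |
| 100 | 23.0 / 77.0 | 0.0689 | 0.0666 | 84% |

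So about 19 to 21 PIB cases are expected instead of the planned 23. Part of that gap is not due to the mix: 23 of 92 is 25%, while the plan's 23% gives 92 × 0.23 = 21.2 even at the stated minimum.

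**The case against.** **The sizes may be group targets.** The article gives a number for each group. The recruitment sentence can be read as naming the populations in scope, and "all patients were recruited at the same time" can mean concurrent enrolment across centres. Fig. 1 is not shown, and a closure rule could sit in the full protocol. This stands as far as it goes: 100/120/180 could be reached by filling groups separately, so a reader should not infer that these sizes are unattainable. But the article states no such rule, and its recruitment sentence points the other way. Under this reading, at the reported mix, the non-LOAPT group would reach 180/0.9 = 200 recruits after 200/2.5 × 5 = 400 eligible patients, while operated LOAPT would need about 556. Late patients would then come mainly from one group, and calendar time could become a confounder. That is a risk of this option only, not a defect shown in the plan.

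**The 10% may not apply to PIB.** The minimum of 92 comes only from the AUC aim. PIB is a postoperative event, and the loss is loss during follow-up. This is a fair limit: without loss the comparison is 90 against 92, which is small for approximate ratios. The gap to 100 remains.

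**All objectives might seem underpowered because of this.** The documents do not support that. The plan's own operated LOAPT needs are 78 for mortality and 70 for PIB, and 81 exceeds both. With the pooled two-proportion formula, mortality power (30% v 45%) is 57.5% at 81/121.5 but already 56.0% at the plan's own 78/118. That weakness comes from the 196 itself, a separate error. For PIB (23% v 10%), power is 82.7% at 90/225 and 79.0% at 81/202.5, against 73.7% at the plan's 70/177, so the reported mix does no harm relative to the plan's own calculation.

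**Conclusion.** The point holds in a limited form. The planned groups are inconsistent with the plan's own case mix, and the article offers no mechanism to bridge the two. Expected operated LOAPT numbers are about 90, or 81 with full loss: 10% to 19% below the target of 100, and 2% to 12% below the minimum of 92. For the AUC aim this means power of roughly 75% to 79% instead of the 80% to 84% that 92 to 100 patients would give at the same PIB rate.

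This rests on three assumptions: the 2019 ratios persist, groups fill as patients arrive, and the PIB rate is 23%. The mismatch in ratios does not depend on the loss allowance; the size of the shortfall does. The other two groups meet their minima either way. The low power of the mortality comparison should not be counted here.

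**What to change.** Choose one of two statements in the sample-size paragraph and carry it into the Fig. 1 numbers.

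1. **Groups follow the case mix.** Give the expected sizes for 450 recruits as about 90/135/225 (81/122/203 if 10% are lost). State the AUC power or confidence-interval width at 90 and 81, using one PIB rate throughout. Say whether the 10% loss is expected to affect PIB ascertainment.
2. **Groups are targets.** Say that 100/120/180 are separate targets and that each group closes when full. Reconcile this with the Study design sentence on recruiting all eligible patients, and adjust both comparisons for enrolment period.

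The first option needs no extra patients: it costs rewording and a slightly less favourable stated figure for the AUC aim. The second costs rewording and one added adjustment, and at the reported mix it means continuing until about 556 eligible patients have presented. Neither repairs the mortality sample size, which needs its own correction.
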